### Participants

2.2.

Participants will be recruited among patients who have been admitted to the neurorehabilitation unit of the rehabilitation hospital. The inclusion criteria are as follows: (1) cognitive impairment secondary to a first-ever ABI, as evidenced by a Clinical Dementia Scale (CDR) score of 0.5 – 1; (2) a diagnosis of ABI > 3 months ago with medical records and/or brain imaging; (3) no history of prior ABI; (4) upper limb muscle strength of ≥ 3 on the medical research council scale, indicating suitability for training and assessment; (5) age >19 years. The exclusion criteria are: (1) known cognitive impairment prior to ABI; (2) severe aphasia or cognitive communication disorder precluding cognitive intervention, including MAT and CCT, or assessment; (3) neurological or psychiatric disorders other than ABI; (4) severe depression (Geriatric Depression Scale-short form score of ≥8); (5) uncontrolled medical illnesses, such as severe cardiac or respiratory disease. The exclusion criteria are as follows: (1) known cognitive impairment prior to ABI; (2) severe aphasia or cognitive communication disorder which precluded cognitive intervention including MAT and CCT or assessment; (3) neurological or psychiatric disorder other than ABI; (4) severe depression [Geriatric Depression Scale-short form ≥8]; (5) uncontrolled medical illness such as severe cardiac or respiratory disease. The experimental protocol was approved by the ethics committee of the rehabilitation hospital (IRB no. NRC-2015-04-032). Sample size calculation was not possible because the effects of the VR-MAT on cognitive function have not yet been reported. Therefore, we have set the sample size to 12 for each arm, in accordance with the minimum number recommended for pilot trials (46, 47). In total, considering a potential participant attrition rate of 20%, we aim to recruit 24 participants for this pilot study.

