### Outcome measurement

2.5.

Baseline demographic characteristics, including sex, age, diagnosis of ABI, duration after ABI, side of brain lesion, and education, will be collected. Additionally, neuropsychological outcomes will be measured for each participant at baseline, after 20 sessions (4 weeks), and after 40 sessions of intervention (after 20 sessions of alternative intervention; 8 weeks) by a blinded neuropsychologist. We will collect data on neuropsychological outcomes in two ways: global cognitive function and executive function, which are specific targets of VR-MAT. All of the cognitive function tests will be administered in Korean. Additionally, we will obtain VR-MAT behavioral data, which is previously explained, and functional infrared spectroscopy (fNIRS) data (Table 1).

**Table 1 tab1:** List of outcome measurements.

Global neuropsychological assessment	Mini-mental status examination (MMSE)
Clinical dementia rating (CDR)
Global deterioration scale (GDS)
Subjective memory complaint questionnaires (SMCQ)
Executive function assessment	Trail making test (TMT)
	TMT-black & white (TMT-B&W)
	Attention-switching Task (AST)
	Stop signal task (SST)
	Spatial working memory (SWM)
VR-MAT behavioral measures	VR-MAT response time
	VR-MAT accuracy
Functional near-infrared spectroscopy	Oxygenated hemoglobin
	Deoxygenated hemoglobin
	Total hemoglobin concentration
	Oxygen level change

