### Statistical analysis

2.7.

We will perform descriptive statistical analysis of the general demographics of the study participants. We define completers as participants who finish 20 sessions of either intervention (VR-MAT or CT) and undergo measurements at 4 weeks of intervention. The statistical analysis will be conducted on an intention to treat basis and the last observation carried forward method will be used to complete the data. Adherence will be reported as the number of completers among enrolled participants. For neuropsychological assessments, a comparative analysis between two different intervention sequences (VC or CV) will be performed and the carry-over effects will be tested using *t*-tests on the change in each sequence for all crossover endpoints (70, 71). For variables with insignificant carry-over effects, the changes in variables during specific interventions from either sequence will be combined and compared. For patients with significant carry-over effects, we will compare the changes in specific interventions during the first period (20 sessions of either intervention). Comparisons between interventions will be performed using a two-tailed *t*-test or the Mann–Whitney *U* test, depending on normality. For music behavior responses obtained from the VR-MAT data, we will perform a two-way repeated-measures analysis of variance (ANOVA) on level (levels 1, 2, 3, and 4) and time (pre, day 8, day 15, and post) with Bonferroni *post-hoc* comparisons.

Repeated measures of correlation between executive function assessment and VR-MAT variables will be examined to determine the linear relationship between paired repeated data using the R package rmcorr from R.3.6.1 (72). The independent variables will remain the same for the analysis of fNIRS data, and the dependent variables will be the PRIs obtained from all channels. All analyses will be performed using the software package R.3.6.1,^1^ and the level of significance will be set to 0.05.

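### The first-period fallback compares raw changes and leaves the collected baseline unused as a covariate, a modest and avoidable loss of precision at 12 per arm

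*Protocol article*

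**What the plan says.** The Statistical analysis section sets a two-step rule for the neuropsychological outcomes. Carry-over is tested first, for every crossover endpoint. Where it is not significant, changes under each intervention are pooled over both sequences. The other branch opens with "For patients with significant carry-over effects" (I read this as variables, as in the sentence before it) and continues: "we will compare the changes in specific interventions during the first period".

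The test is then named: "Comparisons between interventions will be performed using a two-tailed" t-test or, depending on normality, the Mann–Whitney U test. No baseline covariate is named for any neuropsychological comparison. For alpha, "the level of significance will be set to 0.05".

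On data, the Outcome measurement section states that "neuropsychological outcomes will be measured for each participant at baseline, after 20 sessions (4 weeks), and after 40 sessions of intervention". On size, the Participants section states that "we have set the sample size to 12 for each arm", with no power or precision calculation behind it.

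The article therefore fixes the fallback method. It is not a detail left to an unseen analysis plan.

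**The concern.** In the first period nobody has yet received the other intervention, so this comparison is free of carry-over by design. It is also the smallest comparison in the trial: 12 against 12, between participants.

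A change score subtracts the whole baseline value, however weakly baseline predicts week 4. When the correlation is well below 1, that subtracts too much and adds baseline noise to the estimate. A model with baseline as covariate estimates how much to subtract. In a pilot with no power calculation, interval width limits what can be learned for the next trial, so a free reduction in width is worth having.

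**Working it through.** **The plan's own figure.** The article gives no effect size, SD, correlation or power, so there is no precision figure to reproduce. The only stated size is 2 × 12 = 24 participants. Whether 24 also allows for the stated 20% attrition is a separate matter.

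**Inputs.** From the article: n = 12 per arm, 1:1 allocation, two-sided alpha 0.05. Assumed, because the article does not give them: a correlation r between baseline and week 4 (shown over a range), equal SDs s at both times, and a linear relation with a common slope. Results are in units of s.

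**Formulas.**
- Comparison of changes: variance = 2(1 − r) × 2/n, with 2n − 2 = 22 degrees of freedom, t = 2.0739.
- Baseline-adjusted comparison: variance = (1 − r²) × (2/n) × [1 + 1/(2n − 4)], with 21 degrees of freedom, t = 2.0796. The bracket is the cost of estimating the slope; at n = 12 it is 1 + 1/20 = 1.05.
- Variance ratio, adjusted to change = 1.05 × (1 + r)/2.

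**Worked case, r = 0.5.**
- Change: half-width 2.0739 × √(2 × 0.5 × 2/12) = 2.0739 × 0.4082 = 0.847.
- Adjusted: half-width 2.0796 × √(0.75 × 2/12 × 1.05) = 2.0796 × 0.3623 = 0.753.
- Ratio 0.753/0.847 = 0.89, so 11% narrower. Variance ratio 0.7875, and 1/0.7875 = 1.27, so worth 27% more participants.

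**Range at 12 per arm.**

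| r (assumed) | Variance ratio | Half-width, change | Half-width, adjusted | Interval | Worth, in participants |
|---|---|---|---|---|---|
| 0.3 | 0.68 | 1.00 | 0.83 | 17% narrower | +46% |
| 0.5 | 0.79 | 0.85 | 0.75 | 11% narrower | +27% |
| 0.7 | 0.89 | 0.66 | 0.62 | 5% narrower | +12% |
| 0.8 | 0.94 | 0.54 | 0.52 | 3% narrower | +6% |
| 0.9 | 1.00 | 0.38 | 0.38 | no gain | 0 |
| 0.95 | 1.02 | 0.27 | 0.27 | 1% wider | −2% |

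Break-even in variance is where 1.05 × (1 + r)/2 = 1, that is r = 2/1.05 − 1 = 0.905.

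**Power, for an illustrative true difference of 0.8 SD** (not from the article), change against adjusted: 47% and 56% at r = 0.5; 68% and 72% at r = 0.7; 84% and 86% at r = 0.8.

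**Validity check.** In simulation with no treatment effect, both methods rejected in about 5% of trials at each r from 0.3 to 0.9, and the simulated variance ratios agreed with the table.

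**The case against.** **It is only a fallback.** Without true carry-over, each outcome reaches it with probability of about 5%, and the default pooled comparison also uses raw changes. This limits the weight of the point. But many endpoints are tested: with 15 independent tests the chance that at least one is triggered is 1 − 0.95¹⁵ = 54% (illustrative, since the endpoints are correlated). The article describes no washout, so genuine carry-over is also possible.

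**It is a preference, not an error.** This stands. Nothing is misstated, and the test is valid under randomisation.

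**A linear model would discard the safeguard for non-normal outcomes.** This stands too, and it shapes the fix. TMT times and SWM errors may be skewed, and GDS is a seven-stage scale. Entry at CDR 0.5–1 leaves the global CDR two possible baseline values. The figures above apply to the t-test case only.

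**Stronger readings that the article does not support.**
- A reader might infer that chance baseline imbalance is a further harm, or a bias. It is the same loss seen another way. At r = 0.6, before the cost of estimating the slope, the variances are 2 × 0.4 × 2/12 = 0.133 (change) and 0.64 × 2/12 = 0.107 (adjusted). The gap of 0.027 is the square of 0.4 × √(2/12) = 0.163, which is the shift from a one-SD imbalance. It must not be counted twice.
- A reader might take the large-sample ratio (1 + r)/2 and claim 33%, 18% or 11% more participants at r = 0.5, 0.7 or 0.8. That leaves out the slope cost at 12 per arm.
- A reader might shrink the arms for 20% attrition. Under intention to treat with last observation carried forward, all randomised participants stay in the comparison.

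**Conclusion.** The point holds as a matter of efficiency. The fallback leaves unused a covariate that the trial already collects. At 12 per arm this makes the 95% interval about 11%, 5% or 3% narrower at a correlation of 0.5, 0.7 or 0.8, and brings nothing at about 0.9 or above. The correlation is an assumption, so the size of the gain is uncertain; the worst case shown costs about 2% in variance.

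It would be wrong to conclude that adjustment makes the fallback sound. The first-period result is reported only after a significant carry-over test, and that selects it. In simulations with no effects, 12 per arm, equal correlations and a pretest on total week-8 change, type I error given a significant pretest was about 15–17% for change scores and about 8–13% for the adjusted model, at r from 0.5 to 0.8. The article does not fully define the carry-over test, so these figures are illustrative. Adjustment lessens the problem without removing it, and a nominal 95% interval on this branch needs that caveat. Nor does it cure last observation carried forward, which gives a zero change to anyone without a week-4 score.

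**What to change.** In the Statistical analysis section, replace the first-period test as follows.

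- Roughly continuous outcomes: a linear model of the week-4 score on randomised sequence, with the baseline score of the same test as covariate. Report the adjusted difference with its 95% confidence interval.
- Skewed or coarse ordinal outcomes (for example TMT times, SWM errors, global CDR, GDS): a transformed or rank-based baseline-adjusted analysis, or the Mann–Whitney test where baseline hardly varies. State in advance which outcomes take which route.
- Add that first-period results chosen by the carry-over test are subject to selection, and that their intervals should be read accordingly.

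Cost: a few sentences, no new data, one degree of freedom, and at most about 2% in variance if the correlation is very high. The carry-over pretest and the missing-data rule need their own decisions.

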## Discussion

3.

Instrumental music playing combined with VR technology might be a promising strategy for increasing the effectiveness of MAT by providing individualized and systematic interventions. This study aims to develop a replicable therapeutic protocol using an active music-playing platform. This topic is essential, considering that individuals need customized training programs suited to their functional levels and musical preferences. In addition, an increasing number of individuals require remote access to music-based attention programs, specifically those with restricted mobility. Moreover, our system can be used as a cognitive function measurement tool because music behavior data will be recorded with regard to accuracy and response time across all sessions. The data will be used to set up an individualized rhythm, determine whether to proceed to the next level of trial, and track changes over time.

The effectiveness of the system will be explored using cognitive outcome measures, including global and specific cognitive function test, especially executive function. Attention is a key component of executive function, as attention direct cognitive resources toward more important stimuli in order to sustain information processing and engaging and disengaging attention is linked to flexibility or inhibitory control [3; 4]. Thus, our cognitive outcomes could demonstrate how improvements in attentional abilities impact executive function, moreover global cognitive function. In addition, fNIRS data employ multifaceted variables of cerebral hemodynamics to indicate a PRI, which can provide interpretable information in terms of relationships and intensity changes over time. Therefore, the present study will contribute to increasing the scientific rigor of understanding how active music playing can affect cognitive function and cerebral hemodynamic responses, thus demonstrating its efficacy in cognitive rehabilitation. This specific study protocol enables music therapists to measure and quantify musical responses and clearly indicates how changes in musical responses are related to and can lead to cognitive enhancement. In addition, the evaluation and training protocols that we designed are readily applicable to music therapy in medical and rehabilitation settings if the use of electronic media and information technologies readily gains acceptance.

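### Completing the VR-MAT performance data by last observation carried forward flattens the learning curve that the level-by-time ANOVA is meant to estimate

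*Protocol article*

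**What the plan says.** Protocol article, section 2.3.1, schedules four evaluations of VR-MAT performance, on days 1, 8, 15 and 22 of the VR-MAT period. Each yields accuracy and response time.

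Section 2.7 analyses these by a "two-way repeated-measures analysis of variance (ANOVA) on level (levels 1, 2, 3, and 4) and time", "with Bonferroni *post-hoc* comparisons", and states that the same independent variables are used for the fNIRS response intensities (PRI).

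Missing data are covered by one sentence for the analysis as a whole, which adopts intention to treat and adds that "the last observation carried forward method will be used to complete the data". Completers are defined in the same paragraph, but their stated use is descriptive: "Adherence will be reported as the number of completers among enrolled participants".

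Section 2.2 sets 24 participants, 12 per arm, "considering a potential participant attrition rate of 20" per cent. Under section 2.1, participants in the CV sequence have 20 sessions of conventional training before VR-MAT begins.

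**The concern.** The time effect in this ANOVA is the learning curve on the drumming task. LOCF assumes that a participant who leaves would have stayed at the last recorded level. That is the opposite of what a training study expects, so the imputation works directly against the quantity being estimated. The filled values then enter the error term as if they had been measured.

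The rule also has a gap. A CV participant who leaves during conventional training has no VR-MAT value at all, so LOCF cannot deliver the stated intention-to-treat basis for this analysis.

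At stake are the size and shape of the practice effect, its standard error, and the parallel PRI analysis.

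**Working it through.** **Inputs from the article.** N = 24; anticipated attrition 20%; four evaluations, hence three intervals; level of significance 0.05 ("the level of significance will be set to 0.05"). The article gives no expected slope, exit time or covariance, so those below are assumptions.

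**1. The plan's own figure.** When sphericity holds and the data are complete, the planned F tests keep their nominal level. Simulation (20,000 null data sets each at n = 19 and n = 24) gave a size of 0.048 to 0.052 against 0.05. The method is sound on complete data; the question is what LOCF does to incomplete data.

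**2. Expected number still observed.** 24 × 0.8 = 19.2, about 19.

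**3. Effect on the day 1 to day 22 gain.** Let a be the share who leave during VR-MAT, s the rise per evaluation, and k the number of intervals seen before leaving (0, 1 or 2). The gain without loss is 3s. LOCF reports

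(1 − a) × 3s + a × k × s.

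With s = 5 points (assumed), the gain without loss is 15:

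| Last evaluation seen | a = 10% | a = 20% |
|---|---|---|
| day 1 (k = 0) | 0.9 × 15 + 0.1 × 0 = 13.5 | 0.8 × 15 + 0.2 × 0 = 12 |
| day 8 (k = 1) | 0.9 × 15 + 0.1 × 5 = 14 | 0.8 × 15 + 0.2 × 5 = 13 |
| day 15 (k = 2) | 0.9 × 15 + 0.1 × 10 = 14.5 | 0.8 × 15 + 0.2 × 10 = 14 |

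The relative shortfall is a × (3 − k)/3, whatever the slope. At a = 20% it is 20%, 13.3% or 6.7% of the gain. The 10% column allows for losses outside the VR-MAT period: a VC participant who leaves in the second period already has complete VR-MAT data. The calculation assumes a linear rise and that leavers would have improved like the others.

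**4. Uncertainty.** With LOCF the time test uses 3 × (24 − 1) = 69 error degrees of freedom. About 19 fully observed participants support 3 × (19 − 1) = 54. The difference comes from values that were not measured.

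**5. Where LOCF has no input.** For a CV participant, the first VR-MAT evaluation follows the conventional training period. Leaving in that period means none of the 16 level-by-time cells is filled and there is no earlier VR-MAT value to carry.

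**6. Which mixed model.** A participant random intercept alone forces equal correlation over all 16 cells. Under assumed covariances (correlation over time AR(1) 0.7 and 0.85, level SDs from 1 to 2, between-level correlation 0.3 to 0.7, n = 19 and 24, complete data), simulated type I error was:

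| Analysis | time | level by time |
|---|---|---|
| planned ANOVA | 6–7% | 7–9% |
| random intercept only | 2–33% | about 0% |

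Adding participant-by-time and participant-by-level effects gives each main effect its own error term, as the planned ANOVA does.

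**The case against.** The strongest reply is that LOCF is a declared rule, that these are training-performance data in a pilot of 24, and that the loss is two points out of 15 under a slope the article does not give. This stands as a limit on importance. The randomised comparison rests on the neuropsychological tests, and the ANOVA describes change within the VR-MAT period. It does not remove the bias, whose direction follows from the rule whenever performance improves.

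A reader might infer four stronger faults. The article does not support them.

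- **That the ANOVA is complete-case.** The LOCF sentence covers the whole statistical analysis, and completers serve only to report adherence.
- **That Level 3 and 4 cells will be empty at day 1.** The Discussion says that performance data help to "determine whether to proceed to the next level of trial", which reads most naturally as progression in training. No section withholds a level at an evaluation, and section 2.7 plans all four levels at every time.
- **That leaving out sequence inflates the error rate.** Level and time are both within-participant factors. In simulation, an omitted sequence main effect left the size of the time test at 0.048 to 0.052. An omitted balanced sequence-by-time effect made it conservative (0.023 and 0.003).
- **That the plan assumes sphericity.** The article is silent, and a correction is a detail that an article may leave to the full plan.

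**Conclusion.** The point holds as one about LOCF. Filling the cells of a level-by-time analysis by carrying values forward biases the day 1 to day 22 learning curve toward no change and understates its uncertainty. Under the assumed 5-point rise per evaluation, the reported gain is 13 instead of 15 when 20% leave after day 8, and 12 to 14.5 over the range shown. These sizes rest on an assumed slope and on assumed timing of loss; only the 20% attrition and the four-visit schedule come from the article. The rule also fails for CV participants who leave before VR-MAT starts. The consequence is moderate: it concerns the behavioural learning curve and, where the same factors are used, the PRI analysis.

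**What to change.** In section 2.7, replace LOCF for accuracy and response time, and for PRI where the same factors apply, with a linear mixed model fitted to all observed cells:

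- **Fixed effects:** level, time and level by time, with sequence and sequence by time to allow for CV participants' prior conventional training.
- **Random effects:** participant, participant by time and participant by level, or another prespecified covariance at least this flexible. Do not use a random intercept alone.
- **Inference:** Kenward-Roger or Satterthwaite degrees of freedom, keeping the planned Bonferroni contrasts.
- **Analysis set:** state that participants with no VR-MAT evaluation cannot contribute, and report their number by sequence.

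The model relies on data being missing at random given what was observed, which should be stated. It keeps every partly observed participant but cannot recover those never evaluated. The cost is a change of wording and another R function, with no new data. The small downside is that the covariance structure must be fixed in advance, with a stated fallback, because it may need simplifying at n = 24.

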### Study design

2.1.

The present study will be conducted as an assessor-blinded, randomized, controlled trial with a crossover design at a rehabilitation hospital. Participants will be randomly allocated to either the treatment sequence: VR-MAT first and second with conventional cognitive training (CT) (VC group), or in the opposite order (CV group) with an allocation ratio of 1:1 using a computer-generated randomization table. The crossover design is selected because the participants need to serve as their own control group to minimize confounding effects on cognition, which might be markedly affected by a person’s traits, which is not intended by the intervention. In addition, it might be beneficial for the statistical efficiency of this pilot trial, in which VR-MAT had not been attempted for patients with ABI.

Each VR-MAT or CT training period will last 4 weeks with five 30-min intervention sessions per week, resulting in a total of 20 sessions. Therefore, each participant will have received a total of 40 sessions of the intervention, comprising 20 sessions of VR-MAT and 20 sessions of CT. The randomized group assignments were concealed in consecutively numbered sealed opaque envelopes placed in a plastic container. The allocated group will then be determined by the sequential opening of the envelopes after obtaining written informed consent from the participants. Participants will receive a conventional inpatient rehabilitation program (1 h of physical therapy or 30 min of occupational therapy); however, they will not receive a cognitive intervention. Outcome measurements will be performed by a researcher blinded to the group assignment.

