#### VR-MAT behavioral data

2.3.1.

We will evaluate the VR-MAT performance four times [pre (day 1), mid1 (day 8), mid2 (day 15), and post (day 22) sessions]. We will obtain (1) the VR-MAT performance accuracy, which is defined as the number of matched strokes divided by the total number of strokes, and (2) the VR-MAT response time (RT), which is the time required for the matched strokes. No background music will be played during the evaluation sessions.

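### The time effects on VR-MAT performance and, on the most natural reading, fNIRS PRI are uncontrolled before-after changes, so they should be labelled descriptive and kept out of the efficacy claim

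*Protocol article*

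**What the plan says.** Section 2.1 of the protocol article describes an "assessor-blinded, randomized, controlled trial with a crossover design at a rehabilitation hospital", with 1:1 allocation to VR-MAT then CT (VC) or CT then VR-MAT (CV). It justifies the crossover because "the participants need to serve as their own control group to minimize confounding effects on cognition". On duration it says "Each VR-MAT or CT training period will last 4 weeks with five 30-min intervention sessions per week".

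Section 2.3.1 sets the performance evaluations: "We will evaluate the VR-MAT performance four times [pre (day 1), mid1 (day 8), mid2 (day 15), and post (day 22) sessions". It gives no such evaluation for the CT period.

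Section 2.7 then treats the outcome families differently:

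- **Neuropsychological tests:** "For neuropsychological assessments, a comparative analysis between two different intervention sequences (VC or CV) will be performed". The carry-over test and the comparison between interventions follow from this sentence.
- **VR-MAT accuracy and response time:** a two-way repeated-measures ANOVA "on level (levels 1, 2, 3, and 4) and time (pre, day 8, day 15, and post", with no term for intervention, sequence or period. VR-MAT variables are also correlated with the executive function tests.
- **fNIRS:** "The independent variables will remain the same for the analysis of fNIRS data, and the dependent variables will be the PRIs obtained from all channels".

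The Discussion (section 3) says the study will add rigour to "understanding how active music playing can affect cognitive function and cerebral hemodynamic responses, thus demonstrating its efficacy in cognitive rehabilitation".

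**The concern.** A time effect inside the VR-MAT period is a single-arm before-after change. Participants can enter from just over 3 months after injury, when some may still be recovering. They receive physical or occupational therapy alongside the intervention, and they take the same performance evaluation four times. Each of these could move scores in the direction expected of training.

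The crossover was chosen so that participants would act as their own controls, yet the stated models for these two outcome families do not use that control. A significant time effect on PRI could then be reported as an effect of music playing on cerebral haemodynamics, although the analysis cannot tell it from the natural course. This is a matter of the models the article states, not of detail left to a fuller plan.

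**Working it through.** **1. Which outcomes are compared with CT?**

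| Outcome family (Table 1) | Analysis in 2.7 | Compared with CT? |
|---|---|---|
| Global and executive function tests | VC/CV comparison, carry-over test, VR-MAT against CT | Yes |
| VR-MAT accuracy and response time | Level × time ANOVA; correlation with executive tests | No |
| fNIRS PRI | Same independent variables | No comparison stated |

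The fNIRS sentence comes straight after the one on repeated-measures correlation, so what it refers back to is not certain. Level and time are the only independent variables that 2.7 sets out as model factors, and level exists only in VR-MAT. Neither reading adds a comparison with CT.

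**2. How large could the problem be?** The article gives no drift, SD or power for these outcomes, so there is no stated figure to reproduce. What follows is an illustration under assumptions.

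- Inputs from the article: 24 participants, four time points, significance level 0.05.
- Assumptions: no training effect; a straight-line drift of g from first to last evaluation, in SD of the pre-post change; independent errors with variance 0.5 at each time point, so that the change has SD 1; scores averaged over level.
- Deviations of the four time means from their average are −g/2, −g/6, g/6 and g/2. Their squares sum to (1/4 + 1/36 + 1/36 + 1/4)g² = (5/9)g².
- Noncentrality of the time test: λ = 24 × (5/9)g² / 0.5 = 26.67g², with 3 and 3 × 23 = 69 degrees of freedom.

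| Assumed drift g | λ | Rejection, noncentral F | Rejection, simulation (20,000 runs) |
|---|---|---|---|
| 0 | 0 | 5% | 5.0% |
| 0.25 | 1.67 | 16% | 15.8% |
| 0.5 | 6.67 | 54% | 53.7% |
| 0.75 | 15.0 | 90% | 89.6% |

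With 20% attrition (24 × 0.8 = 19.2, so 19 participants) the simulated rates at the last three drifts are 13%, 43% and 81%.

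**3. What could the randomised sequences offer?** The last VR-MAT evaluation in VC is on day 22. The first in CV follows 4 weeks of CT (4 × 7 = 28 days), so about day 29 if VR-MAT starts at once. The gap is 29 − 22 = 7 days. A contrast of these two evaluations would therefore be close in time since enrolment, but it sets a fourth evaluation after weeks of drumming against a first.

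Precision of a two-group contrast at 12 per sequence, 22 degrees of freedom: 2.074 × √(2/12) = 0.85, so a 95% CI of about ±0.85 SD of the score. This unit is the SD of the score, not of the change used in step 2.

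**The case against.** The strongest reply is that nobody proposes the VR-MAT time effect as an efficacy test. The Discussion says effectiveness will be explored with the cognitive measures, which are compared with CT. The Abstract presents accuracy and response time as an evaluation of VR-MAT performance and gives fNIRS an exploratory role. A level × time ANOVA on a trained task is an ordinary learning curve. This stands for the behavioural scores: the efficacy sentence does not name them. It does not stand for fNIRS, because that sentence names haemodynamic responses and follows directly on the description of PRI and its changes over time.

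A second reply is that the fNIRS model and recording schedule may sit in a fuller document. That is fair. The article gives no fNIRS schedule, so one cannot say that data for a controlled PRI contrast are already being collected.

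A reader might also infer that the crossover already supplies a clean control, and that comparing VC's last evaluation with CV's first would isolate the training effect. The documents do not support this. That contrast reduces confounding by recovery, but familiarity stays fully bundled with training and the two evaluations are about a week apart. Nor can one set the rejection rates above against a nominal 5% for that contrast: familiarity would inflate it too, and the units differ.

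**Conclusion.** The point holds in a limited form. For VR-MAT accuracy and response time, and on the most natural reading for PRI, section 2.7 states only within-period analyses, which cannot attribute a time effect to training. The Discussion goes too far in counting the haemodynamic results towards efficacy. The neuropsychological comparison with CT is untouched, so it would be wrong to infer that the trial has no controlled efficacy analysis.

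The size is unknown. The range of about 16% to 90% false rejection rests on assumed drifts of 0.25 to 0.75 SD of change, a straight-line drift and independent errors; it shows sensitivity and is not a forecast. The conclusion does not depend on it. The change is worth making because it alters what the trial may conclude at almost no cost.

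**What to change.** 1. In 2.7, state that the time effects on VR-MAT accuracy, response time and PRI are descriptive: task learning for the behavioural scores, within-period change for PRI. In the Discussion, limit efficacy wording to outcomes compared with CT.
2. In 2.7, name the independent variables meant by the fNIRS sentence. Where recordings exist at matching times in both sequences, add a between-sequence VR-MAT versus CT contrast of PRI with a 95% CI. If they do not exist, item 1 suffices for PRI.
3. If VC's last evaluation is compared with CV's first for VR-MAT scores, label the contrast exploratory. State that it compares practised with first-time participants at about day 22 and day 29, so it reduces confounding by recovery without removing familiarity.

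Items 1 and 3 need only wording and at most one extra contrast on evaluations already scheduled. Item 2 adds a contrast only if suitable recordings exist. The drawback is imprecision: about ±0.85 SD of the score with 12 per sequence.
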